### Blinding

It is not possible to blind the intervention in this type of study. The measurement of the primary endpoint, degree of healing, will be conducted by nurses who are unaware of the type of intervention applied to the patient. The analysis will be performed by practitioners who are unaware of the assignment.

### Intervention

#### Control group

Standard clinical practice that consists of healing the wound (assessment, cleaning, disinfection, debridement and topical treatment) and application of simple compression therapy with a light compression, single-layer elastic bandage (crepe bandage).

#### Intervention group

The standard practice in healing will be conducted, modifying the application of compression therapy, which in this case will be multilayer, using 2 layers.

All patients will be provided hygienic-dietary counselling and information on adverse signs and symptoms.

Both interventions will be performed in the health centre or at home, according to the patient’s needs.

The sequence of visits is listed in Fig. 2.

**Fig. 2 Fig2:**
[figure not shown]
Sequence of visits in Control and Experimental Group

The schedule of visits is shown in Table 1.

**Table 1 Tab1:** Schedule of visits

	Baseline visit Day 0	Visit 1 Day 1	Visit 2 Day 15	Visit 3 Day 30	Visit 4 Day 45	Visit 5 Day 60	Visit 6 Day 75	Visit 7 Day 90 End of follow-up
Verification of inclusion criteria	x							
Patient has signed the informed consent	x							
Randomisation	x							
Intervention		x	x	x	x	x	x	x
Resverch assessment		x	x	x	x	x	x	x
CCVUQ-e questionnaire		x						x
Collecting data on adverse reactions			x	x	x	x	x	x
Healing complete			x	x	x	x	x	x
Sociodemographic variables	x							
Prognostic variables		x						
Variables related to healing		x	x	x	x	x	x	x

### Training

The participant nurses will receive an standardized training to minimize, as much as possible, the differences in the in the implementation of the 2 interventions. The method for performing the control technique will be consistent, and training will be provided to the nurses participating in the study on multilayer compression bandages. Both techniques will be documented in writing and supplemented with images.

To avoid differences in the assessment criteria as much as possible, prior training will be conducted for both groups. The blinded evaluators will also be trained.

### Variables

#### Outcome variables

The main outcome variable is the Complete healing at 12 weeks of follow-up: (yes/no). *complete and sustained epithelialisation for at least 2 weeks. Time elapsed between start of the study and complete healing of the wound (in days).

Secondary outcome variables are: Degree of healing (Resvech 2.0); health-related quality of life for patients with venous ulcers (CCVUQ-e) and presence of adverse reactions.

The RESVECH 2.0 scale was used to monitor wounds [17]. Based on the results of a PhD thesis, it can be used to assess characteristics and evaluate the healing process in all types of chronic wounds. It assesses six parameters: wound size, depth of the affected tissues, status of the edges, type of tissue in the wound bed, level of exudate and inflammation-infection in the wound (presence of biofilm).

The CCVUQe is a specific tool to measure quality of life with venous ulceration [7], recently validated Spanish language version of the questionnaire.

#### Sociodemographic variables

Age, sex, living alone (yes/no), employment status and education level.

#### Variables related to the healing process

Body mass index. Quantitative (kg/cm^2^); underlying disease; ABI; tobacco and alcohol consumption; topical and systemic treatment; patient mobility; time dedicated by patient to walking, exercise and raising the legs above the heart (minutes/day, times/week); intervention group.Time the patient remains with the legs above the heart (minutes/week; times/week).Intervention group: multilayer compression bandages with 2 layers / crepe bandages.

#### Prognostic variables

Location of the ulcer; number of ulcers at the time of the study; time in days of evolution of the venous ulcers before inclusion in the study; recurrent ulcer (yes/no); location where the intervention is performed (home/health centre).

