#### Inclusion criteria

Over 18 years of age.Individuals with a diagnosis of venous ulcers of more than 6 weeks of evolution. If the participant has more than one lesion, the nurse will select the lesion with the highest Resvech score for the study.Presence of an ankle brachial index (ABI) greater than 0.8 and less than 1.3.Individuals who able to follow the demands of the trial and who provide their written informed consent to participate.

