### Sample size

Earlier studies have achieved complete healing rates at 12 weeks of follow-up of 58 % by employing multilayer bandages. For an alpha error of 0.05 and a beta error of 0.2 (80 % power) and to detect a minimum difference of 20 % between the 2 groups, a total of 97 patients will be needed in each group. Estimating a 10 % loss rate at 3 months, at least 108 patients will be included in each study branch.

The patients will be consecutively included in the study. The recruitment will be competitive until the sample size is reached.

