### Analysis

Descriptive analysis of each variable with its corresponding 95 % confidence interval. Normality tests. Description of the profile of patients who withdraw from the study and their reasons for withdrawal.Comparison of the group at the beginning of the trial with regard to their descriptive and response variables and predictors. Bivariate statistical tests will be employed that are suitable for the variable type (qualitative or quantitative).Primary effectiveness analysis: A comparison will be performed of the incidence rates of ulcers with complete healing, using the ratio of incidence rates, with their point estimate and 95 % confidence interval. We will compare the time to complete healing using Kaplan-Meier curves for both types of treatment (log-rank test). To adjust for prognostic factors, we will perform a Cox regression model, with the time elapsed to complete healing as the dependent variable, complete healing as the event and the intervention group as the independent variable. We will include in the model those variables that can act as confounding factors or that can modify the effect.Secondary effectiveness analysis: For each secondary variable, we will apply the appropriate statistical technique based on the character of each variable (qualitative or quantitative) and to the distribution to which they fit (parametric or nonparametric).

The individuals responsible for performing the analysis will be unaware of which intervention each patient included in the study has undergone. All statistical analyses will be performed by intent-to-treat, using the conventional level of statistical significance (0.05).

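### Baseline Resvech 2.0 is scheduled for every patient but is not a listed prognostic variable and is not assured of entry into the primary Cox model, so efficiency may be lost

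*Protocol article*

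**What the plan says.** - **What Resvech measures.** Outcome variables describes the scale thus: "It assesses six parameters: wound size, depth of the affected tissues, status of the edges, type of tissue in the wound bed", followed by exudate and inflammation-infection. It is given one role there, as a secondary outcome.
- **When it is scored.** Table 1 marks it at Visit 1 (Day 1) and at every later visit. Randomisation is marked at Day 0. The intervention is also first marked at Visit 1.
- **Use at entry.** Under Inclusion criteria, if a patient has more than one lesion, "the nurse will select the lesion with the highest Resvech score for the study".
- **Covariate lists.** Prognostic variables reads "Location of the ulcer; number of ulcers at the time of the study; time in days of evolution of the venous ulcers before inclusion", then recurrence and place of care. Neither this list, nor the sociodemographic list, nor the list of variables related to the healing process contains the starting Resvech score or wound size.
- **Primary analysis.** The Analysis section names three components: a ratio of incidence rates; a survival comparison ("We will compare the time to complete healing using Kaplan-Meier curves for both types of treatment (log-rank test"); and a model introduced with "To adjust for prognostic factors, we will perform a Cox regression model". The first two name no covariates or strata. For the third, the stated rule admits candidates for confounding or for effect modification. No component is named as the decisive one.

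**The concern.** The primary endpoint is closure of the wound, and the starting state of that wound is an obvious candidate predictor. The article prints its own prognostic list and says the Cox model adjusts for prognostic factors, yet the list leaves that starting state out.

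The entry rule does not repair the gap. In a randomised trial, a predictor that happens to be balanced between arms does not confound the treatment comparison. A rule framed around confounding can therefore exclude it, although adjusting for a strong predictor gains power even when the arms are balanced. What is at stake is power and precision that could come from a measurement the trial already makes.

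**Working it through.** **1. Reproduce the plan's figure.** Inputs from Sample size: "Earlier studies have achieved complete healing rates at 12 weeks of follow-up of 58" per cent; "to detect a minimum difference of 20" per cent; "For an alpha error of 0.05 and a beta error of 0.2". The control rate is not stated; 0.58 - 0.20 = 0.38 is implied. A two-sided test is assumed because it reproduces the figure. With mean proportion 0.48:

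n = [1.96 × √(2 × 0.48 × 0.52) + 0.842 × √(0.58 × 0.42 + 0.38 × 0.62)]² / 0.20² = 96.8, so 97 per arm.

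Allowing for 10% loss: 97 / 0.90 = 107.8, so 108. Both stated figures reproduce, and power at 97 per arm is 80.1%.

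**2. Variance-reduction approximation.** If the baseline score explains a share R² of the variance in healing, the effective n per arm is 97 / (1 - R²), and 97 × (1 - R²) patients would give the planned power. The document gives no R², so a range is shown.

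| Assumed R² | Effective n per arm | Power | n per arm for 80% |
|---|---|---|---|
| 0 | 97 | 80.1% | 97 |
| 0.05 | 102.1 | 82.1% | 93 |
| 0.10 | 107.8 | 84.1% | 88 |
| 0.20 | 121.3 | 88.1% | 78 |
| 0.30 | 138.6 | 91.9% | 68 |

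**3. Simulation of the Cox model.** The set-up was 97 per arm, exponential healing times, censoring at 12 weeks, a standard-normal baseline score, and marginal healing fixed at 38% and 58%. Expected events are 97 × (0.58 + 0.38) = 93. Two separate simulations were run, A with 3000 trials per setting and B with 1500. The comparator is a Cox model with treatment only. The direction of the score does not affect power, so hazard ratios are shown above 1.

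| Assumed HR per SD of score | Simulation | Unadjusted power | Adjusted power |
|---|---|---|---|
| 1.0 (no effect) | B | 82% | 81% |
| 1.35 | B | 83% | 85% |
| 1.5 | A | 83% | 85% |
| 1.65 | B | 82% | 87% |
| 1.75 | A | 82% | 88% |
| 2.0 | A | 83% | 92% |
| 2.0 | B | 83% | 91% |

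The Monte Carlo standard error is about √(0.8 × 0.2 / 1500) = 1 point in B and less in A, so 82% v 81% in the first row is no difference. In simulation A, the adjusted test rejected in 4.9% of null trials at a hazard ratio of 2.0.

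**4. Where the gain comes from.** In a Cox model it arises mainly because the treatment log hazard ratio conditional on severity is larger than the marginal one, not because its standard error shrinks.

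**5. Timing.** Table 1 documents no scheduled score at Day 0. A score at selection is implied only for patients with several lesions. For a patient with a single ulcer, the first documented score is at Visit 1, the visit at which the intervention is first marked.

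**The case against.** A reader might infer that the whole primary comparison is unadjusted. The document does not support that. A Cox model meant to adjust for prognostic factors sits under the primary effectiveness analysis, and its rule neither names nor excludes Resvech. The rule can also be read as choosing known predictors in advance. In addition, the groups are to be compared at the start on their response variables, and Resvech is one. This stands: the score could enter. What remains is that nothing assures its entry.

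A reader might also infer bias, or that the trial will miss a true 20-point difference. Neither follows. The unadjusted tests are valid, the sample size is right for a two-proportion comparison, and a 20% chance of missing that difference is the beta error the plan accepts. A hazard ratio closer to 1 without adjustment is a marginal effect, not a biased one.

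The comparator can fairly be challenged. The planned Cox model may already contain ulcer duration, number and recurrence. The relevant gain is what Resvech adds to those, and that was not computed. It would be smaller if they carry the same information.

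Finally, naming every covariate is commonly left to an analysis plan, which is not shown. That would answer a complaint about missing detail. It answers this point less well, because the article prints a prognostic list and an entry rule, and both leave the severity score unsecured.

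**Conclusion.** The point holds as a possible loss of efficiency. Baseline Resvech is absent from the prognostic list, is not assured of entry into the Cox model, and plays no part in the rate ratio or log-rank test as described.

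The size rests on an assumed prognostic strength. Against a Cox model with no covariates, the gain is about 2 points of power at a hazard ratio of 1.5 per SD and about 8 to 9 points at 2.0. It is nil if the score predicts nothing and smaller if the listed factors overlap with it. The stated 97 and 108 per arm are not in question.

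It would also be wrong to assume that a score taken before allocation already exists for everyone. Table 1 and the inclusion criteria do not show one for patients with a single ulcer.

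**What to change.** - Add the index ulcer's baseline Resvech 2.0 total score to Prognostic variables.
- In Analysis, pre-specify that score as a continuous covariate in the Cox model, whatever the observed balance, alongside the already listed ulcer duration.
- State whether the adjusted Cox result or an unadjusted result is the primary one.
- Specify that the score used is the one taken before the first study bandage is applied, and before allocation where possible. The first scheduled score falls on Day 1 and randomisation on Day 0.
- Keep reporting the unadjusted rate ratio, Kaplan-Meier curves and log-rank test.

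The cost is a few sentences and no extra patients. No extra assessment is needed if the Visit 1 score is confirmed to precede the bandage; a score before allocation would have to be arranged for patients with a single ulcer. Treatment plus two covariates against about 93 expected events leaves 93 / 3 = 31 events per parameter. The downside is that the Cox hazard ratio becomes conditional on severity, which the text should say.

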### Data collection

During the nursing consultation (in the health centre or at home), the individuals eligible for inclusion in the study will be informed of their eligibility and offered a chance to participate. If they accept, the patients will be checked to see if they meet all the eligibility criteria and will be requested to complete and sign the informed consent. Data collection will be performed every 14 days during the 12-week follow-up or will finish early if the ulcer has healed.

The information will be collected through clinical interviews and wound examinations, and the information will be recorded in the eCRFs. We will record those patients who decline to participate in the study (age and sex), as well as the losses, attrition and their causes. We will also record those patients who withdraw due to the withdrawal criteria.

The researchers will record the severe or unexpected adverse reactions regarding the product and will notify the principal investigator.

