### Aim

The aim of this study is to assess whether multilayer compression bandages with 2 layers are more effective than crepe bandages in the healing of chronic venous ulcers in patients treated in primary care nursing consultations, measured by the incidence rate of ulcers with complete healing at 12 weeks of follow-up in each group.

The secondary objectives are to compare the effectiveness of the multilayer and crepe bandages (based on the degree of healing achieved and measured with Resvech 2.0), assess improvements in quality of life (measured with the Charing Cross Venous Ulcer Questionnaire [CCVuQ-e]) and analyse the sociodemographic, clinical and treatment factors associated with complete healing of venous ulcers.

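### Follow-up quality of life (CCVUQ-e) is scheduled only at Day 90 but data collection stops at healing, so patients healed earlier have no follow-up score or one at an outcome-dependent time

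*Protocol article*

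**What the plan says.** The article lists as a secondary outcome "health-related quality of life for patients with venous ulcers (CCVUQ-e) and presence of adverse reactions", and the Aim section makes improvement in quality of life a secondary objective.

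Table 1 has a row "CCVUQ-e questionnaire" with two crosses: Visit 1 (Day 1) and the column headed "Visit 7 Day 90 End of follow-up". Visits 2 to 6 have none.

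The Data collection section sets the duration of follow-up: "Data collection will be performed every 14 days during the 12-week follow-up or will finish early if the ulcer has healed". It makes no exception for any instrument.

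Healing is defined under Outcome variables as "complete and sustained epithelialisation for at least 2 weeks". Table 1 allows it to be recorded from Visit 2 (Day 15) through Visit 7 (Day 90).

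The Analysis section commits all statistical analyses to intention to treat.

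**The concern.** The schedule and the stopping rule for data collection do not fit together. The only post-baseline questionnaire sits at Day 90, and the rule ends collection for a patient who has healed sooner. Whether a patient provides the score would then depend on the primary outcome, which the bandage is meant to change.

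If healed patients drop out of the quality-of-life data, the arms are compared among those still unhealed. That group is selected after randomisation and differs in size between arms, and any gain in quality of life that comes through healing is left out of the comparison.

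The missing score cannot be inferred from the fact of healing. The questionnaire is answered by the patient, while the trial follows one lesion per patient (Inclusion criteria) in people who may have several. The Background also reports frequent relapse. There is no intermediate CCVUQ-e to carry the analysis. A later analysis plan could not recover questionnaires that were never given.

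**Working it through.** **Inputs.** From Sample size: "Earlier studies have achieved complete healing rates at 12 weeks of follow-up of 58 % by employing multilayer bandages"; the trial is sized "to detect a minimum difference of 20 % between the 2 groups"; alpha 0.05, power 80%, 97 per group, 108 after 10% loss. The crepe rate is taken as 58% − 20% = 38%.

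**1. Reproducing the plan's figure.** Two-sided test of two proportions, no continuity correction, mean rate 0.48:

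n = [1.960·√(2·0.48·0.52) + 0.842·√(0.58·0.42 + 0.38·0.62)]² / 0.20² = (1.385 + 0.583)² / 0.04 ≈ 96.8, so 97. Then 97 / 0.90 = 107.8, so 108.

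Both figures reproduce, so 58% and 38% are the plan's own working rates. Taking 78% for the other arm gives 85, not 97.

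**2. Literal reading, upper bound.** Suppose every healed patient finishes before Day 90.
- Missing: 58% multilayer, 38% crepe; 48% overall, or about 104 of 216 enrolled.
- Retained of 97: 97 × 0.42 = 40.7 and 97 × 0.62 = 60.1.
- Standard error of the mean difference in SD units: √(1/40.7 + 1/60.1) = 0.203, against √(2/97) = 0.144 with all patients. Ratio 1.41.
- Difference detectable at 80% power: 2.80 × 0.203 = 0.57 SD, against 2.80 × 0.144 = 0.40 SD.

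**3. Literal reading, range.** Not all healers finish early. Closure first seen at Visit 6 (Day 75) reaches two weeks at Day 89 and is confirmed at Visit 7, where the CCVUQ-e is given. Let f be the share of healers whose collection ends before Day 90. The article gives no distribution of healing times for its arms, so f is assumed. Missing share = healing rate × f.

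| f (assumed) | Missing, multilayer | Missing, crepe | Gap (points) | Retained of 97 |
|---|---|---|---|---|
| 1.0 | 58% | 38% | 20 | 41 vs 60 |
| 0.9 | 52% | 34% | 18 | 46 vs 64 |
| 0.75 | 44% | 29% | 15 | 55 vs 69 |
| 0.5 | 29% | 19% | 10 | 69 vs 79 |

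**4. What selection removes.** As an illustration, assume healing improves the score by 0.5 to 1.0 SD and the bandage has no other effect. The difference among all patients is 0.20 × 0.5 = 0.10 SD to 0.20 × 1.0 = 0.20 SD. Among unhealed patients it is zero, if healing is unrelated to a patient's underlying quality of life.

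**5. Early-last-visit reading.** If the final questionnaire moves to the patient's own last visit, missingness from this source is 0%. The score is then taken anywhere from the first visit at which healing can be recorded up to Day 90. By Table 1 that is Day 15, or Day 30 if the two weeks must pass between study visits. Unhealed patients are all measured at Day 90. More patients are measured early in the arm that heals faster, so time since baseline differs by arm and by outcome.

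**The case against.** The strongest reply is that the last column of Table 1 is also labelled as the end of follow-up. For a patient who finishes early, the last visit may be that end, with the questionnaire taken there. The article neither states nor excludes this, Fig. 2 is not shown, and a full protocol or case report form may settle it. This stands as a possible reading, and under it nobody lacks a score for this reason. It does not clear the problem, because it replaces missing scores with scores at unequal times that depend on the outcome.

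A reader might infer that every healed patient lacks a follow-up score. The article does not support that: Table 1 marks both healing and the CCVUQ-e at Visit 7, and the two-week requirement pushes some confirmations there. The 41 versus 60 split is therefore an upper bound.

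A reader might also infer that the quality-of-life objective cannot be answered. That too goes further than the article allows. On the literal reading the comparison is biased and restricted to unhealed patients; on the other it is complete but not like-for-like.

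Finally, the SD effects in step 4 are assumptions. On them the full-data comparison would still have low power, since 0.10 to 0.20 SD is well below the 0.40 SD detectable with 97 per arm. That is a fair limit on what the fix buys in precision. It does not excuse a comparison that leaves the effect out.

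**Conclusion.** The point holds for a secondary endpoint. Table 1 and the Data collection section conflict, and under neither reading does the trial obtain the CCVUQ-e from all randomised patients at one common time, which is what an intention-to-treat comparison at the end of follow-up needs.

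On the literal reading, missingness is at most 58% versus 38%, and 29% versus 19% to 52% versus 34% if 50% to 90% of healers finish early. Each of these exceeds the planned 10% loss and differs by 10 to 20 points between arms. These figures rest on the planning rates and the assumed f. On the early-visit reading, missingness is zero and the defect is unequal timing, with a bias whose direction the article does not allow one to state.

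That the literal reading omits any gain through healing needs no assumption about effect size; how large the resulting bias would be does. The primary endpoint and the sample size are not touched.

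**What to change.** Reconcile Table 1 with the Data collection section. State that the early-finish rule does not apply to the CCVUQ-e. Every randomised patient completes it at the common end-of-follow-up time, listed as Day 90, whether or not the ulcer has healed, and the arms are compared at that time. A questionnaire at the healing visit may be added but does not replace the Day 90 one.

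The cost is a sentence in the protocol, a setting in the electronic case report form, and one extra questionnaire contact for patients who healed early, at a time point already scheduled. It changes no treatment. Patients who finished before the change may lack the value; their number should be reported by arm.

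### Data collection stops at healing but the only post-baseline CCVUQ-e is set for day 90, so quality of life is missing or mistimed by healing status, and differently by arm

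*Protocol article*

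**What the plan says.** - **Data collection section:** data are collected every 14 days over the 12 weeks, "or will finish early if the ulcer has healed".
- **Table 1, row "CCVUQ-e questionnaire":** marked at Visit 1 (day 1) and at the last visit, headed "Visit 7 Day 90 End of follow-up". There is no interim form.
- **Aim and Outcome variables:** quality of life on the CCVUQ-e is a named secondary objective and a secondary outcome.
- **Outcome variables:** healing means "complete and sustained epithelialisation for at least 2 weeks".
- **Analysis:** all analyses are by intention to treat.

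The article does not say that healed patients return at day 90, nor that their closing questionnaire is completed when they leave.

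**The concern.** The stopping rule and the questionnaire schedule cannot both be followed for a patient who heals early. The event that ends data collection is the primary outcome, and the trial expects it more often in the two-layer arm. Whether a quality-of-life score exists, or when it is taken, would therefore depend on a post-randomisation result that treatment is meant to change.

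If the score is lost, the observed comparison is confined to patients whose ulcers stayed open. That subset is selected after randomisation and leaves out the patients in whom the bandage worked. If the score is brought forward, the arms are compared at different average times. A questionnaire never given at the common time point cannot be recovered by any later analysis plan.

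**Working it through.** **Inputs from the Sample size section.** The two-layer rate comes from "complete healing rates at 12 weeks of follow-up of 58 % by employing multilayer bandages" and the crepe rate from "to detect a minimum difference of 20 % between the 2 groups": 58% − 20 points = 38%. Alpha is 0.05, power 80% and planned loss 10%.

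**Reproducing the plan's figure.** Two-sided test of two proportions, pooled variance, mean rate 0.48:

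n = [1.960 × √(2 × 0.48 × 0.52) + 0.842 × √(0.58 × 0.42 + 0.38 × 0.62)]² / 0.20² = 96.8, so 97 per arm.

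97 / 0.90 = 107.8, so 108 per arm. Both match the article, so 58% and 38% are the rates it was planned on.

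**Reading A: no form after healing**

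*Upper bound (every healer leaves before day 90).*
- Two-layer: 97 × 0.58 = 56.3 without a form, 40.7 with one.
- Crepe: 97 × 0.38 = 36.9 without, 60.1 with.
- Overall: (56.3 + 36.9) / 194 = 48% missing, against a planned loss of 10%.
- Standard error relative to complete data: √[(1/40.7 + 1/60.1) / (2/97)] = 1.41.

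*Allowing for the two-week rule.* An ulcer first seen closed at Visit 6 (day 75) can be confirmed only at about Visit 7, when the CCVUQ-e is due. Leavers are then those closed by Visit 5 (day 60). Assume a constant healing hazard that reaches the planning rates at day 84 (the article gives no healing-time distribution):
- Two-layer: 1 − 0.42^(60/84) = 46%, about 45 of 97.
- Crepe: 1 − 0.62^(60/84) = 29%, about 28 of 97.

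*A cruder range.* If 20% to 40% of healers still provide a day-90 form, the missing shares run from 46% v 30% (0.58 × 0.8, 0.38 × 0.8) to 35% v 23% (0.58 × 0.6, 0.38 × 0.6).

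*Direction if only patients with a form are compared.* All values here are assumed, in standard deviation units, with every healer missing. Let healing add B to quality of life and let the bandage act only through healing.
- True difference between arms: (0.58 − 0.38) × B = 0.05, 0.10 or 0.20 for B = 0.25, 0.5 or 1.0.
- Unhealed-only difference, no prognostic selection: 0.
- Unhealed-only difference with selection: suppose healing occurs above an arm-specific cut on a standard normal prognosis score. The mean score among the unhealed is −0.931 (two-layer) and −0.614 (crepe), a gap of −0.317. If prognosis correlates 0.2 to 0.4 with quality of life, the difference is −0.06 to −0.13, against the two-layer bandage.
- With an added direct bandage effect of 0.2 and B = 0.5, the true difference of 0.30 shrinks to 0.20 without selection, or to 0.14 to 0.07 with it.

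**Reading B: the form is brought forward to exit**

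No score is lost, but timing differs. Under the same constant hazard, with unhealed patients scored at day 84, the mean time of the form is p × 84 / [−ln(1 − p)]:
- Two-layer: 0.58 × 84 / 0.8675 = 56 days.
- Crepe: 0.38 × 84 / 0.4780 = 67 days.

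If exit comes 14 days after closure, with day 84 as the latest time, the mean is 14 + [1 − (1 − p)^(70/84)] × 84 / [−ln(1 − p)]:
- Two-layer: 14 + 0.5147 × 84 / 0.8675 = 64 days.
- Crepe: 14 + 0.3286 × 84 / 0.4780 = 72 days.

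The two-layer arm would be scored about 8 to 11 days earlier on average, with the time set by healing.

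**The case against.** The strongest objection is that loss is only one reading. Table 1 also labels Visit 7 as the end of follow-up, so the closing questionnaire may be meant for whenever a patient's own follow-up ends. Every healer would then have a score, and the counts under Reading A would not apply. The article also condenses a fuller protocol, which may already say what happens to early healers. Both points stand: the loss figures are an upper bound under one reading. They do not remove the concern, because the article itself states a stopping rule and a fixed schedule that disagree, and the exit-form reading still gives no common time point.

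A reader might also infer that the comparison is certainly biased towards no difference and that the objective cannot be answered. The article does not support that. The direction depends on how the bandage affects quality of life, on prognostic selection and on which patients are analysed. It states none of these, and it specifies intention to treat.

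Three extensions are tempting and should not be made:
- **Adverse reactions:** collecting reactions to the product and the healing process only while the ulcer is under treatment is coherent, and no distortion has been shown.
- **Resvech:** the article gives no score for a healed ulcer, so none can be imputed from it.
- **Choice of test:** the Analysis section ties bivariate tests to the baseline comparison. Preferring a particular model for secondary outcomes is a matter for the analysis plan.

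**Conclusion.** The concern holds in limited form. The Data collection section and Table 1 disagree for patients who heal early, leaving the CCVUQ-e missing or mistimed according to the primary outcome and to a different extent in each arm.

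If the form is lost, at most 58% v 38% lack it; about 46% v 29% is a more realistic figure, resting on the assumed constant hazard and exit only after confirmed closure. An analysis of patients with a day-90 form would then most likely dilute or even reverse a benefit acting through healing, by an amount that depends on values the article does not give. If the form is brought forward, the fault is unequal timing.

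Only the quality-of-life objective is affected. The primary analysis properly ends at healing, and 97 (108 with losses) per arm stands.

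**What to change.** Reconcile the Data collection section with Table 1. State that early closure of data collection does not apply to the CCVUQ-e: every randomised patient completes it at one fixed end-of-study time, healed or not, and the arms are compared on that score in all randomised patients. Name that time once, since 14-day visits over 12 weeks end at day 84 while Table 1 ends at day 90.

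This would raise the expected forms, before ordinary losses, from as few as about 41 v 60 to 97 v 97, leaving only the planned 10% loss. The cost is a wording change and one extra questionnaire contact per healed patient: at most about 56 + 37 = 93 contacts at 97 per arm, or 63 + 41 = 104 at 108 per arm. The change must be made before healed patients pass the end-of-study time, because their scores cannot be collected afterwards.
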